### Participants

Eligibility criteria will be assessed by trained general practitioners in each partner HU. Participants will be eligible if they: (1) have recently recovered (within the last 3 months) from an episode of non-specific LBP (with or without leg pain and of any duration), defined as pain limited to the region between the lower margins of the 12th rib and the gluteal folds to which it is not possible to attribute a specific anatomical or nociceptive physiopathological cause [30, 31]; (2) are aged between 18 and 65 years; (3) are able to read and speak the Portuguese language; (4) have a mobile phone capable of receiving and sending text messages; (5) and do not have any medical contraindication to exercise. Recovery from an LBP episode is defined as having a pain score of “0” or “1” on a 11-point Numeric Pain Rating Scale (NPRS) for, at least, 30 consecutive days [32]. This means that only participants without pain (or minimal pain – 1/10 NPRS) for at least a month are eligible. Additionally, patients will be excluded if they have a diagnosis, or symptoms consistent with, severe depression or other psychiatric condition, if they are pregnant, if they have undergone back surgery in the prior 6 months, or if their proficiency in Portuguese language is inadequate to complete self-reported outcome measures.

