### Recruitment

Potential participants will be recruited from 10 HUs through the collaboration of at least one physiotherapist (PT) from each HU. At the discharge session of the usual treatment programme for an LBP episode, potential participants will receive an information sheet giving details of the MyBack study and will be invited to participate by their PT. Patients who agree to participate will sign the informed consent form and will proceed to a standardized assessment to establish full eligibility. Patients who agree to participate in the study but who have not yet reached the recovery criteria at that time will be contacted every 15 days over a 3-month period, until they reach it. This contact will be made by text message according to the following statement: “On an 11-point scale where “0” means no pain and “10” the worst pain imaginable, in the last month, my back pain was always “0” or “1” (yes / No).

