### Baseline assessment

After eligibility criteria have been confirmed, participants will attend a baseline assessment. All participants will complete the baseline assessment on-site that will include a questionnaire of prognostic factors for LBP recurrence and long-term disability [33–35] and specific instruments to assess pain intensity, functional disability, musculoskeletal health, and health-related quality of life (HRQoL). A description of the study measures is presented in Table 1.

**Table 1 Tab1:** Overview of study measurement

Construct/ Variables	Instrument/ Test	Time point			
		Baseline	Monthly	3, 6 & 12-months	
Demographics	Self-reported questionnaire [33–35]	x			
Clinical		x			
Work Situation**		x	x		
LBP recurrences	The return of LBP with a minimum duration of 24 h, with a pain intensity ≥ 2 on an 11-point numerical scale, preceded by a minimum period of 30 days without pain [32]		x		
Pain intensity**	Numeric Pain Rating Scale (0 to 10) [54, 65]	x	x	x	
Functional Disability**	Roland Morris Disability Scale (0 to 24) [56]	x	x	x	
Musculoskeletal Health (Subdomains: pain severity, physical function, work interference, social interference, sleep, fatigue, emotional health, physical activity, independence, understanding, confidence to self-manage and overall impact)	Musculoskeletal Health Questionnaire (0 to 56) [60, 66]	x		x	
Health-related Quality of Life	EuroQol, 5 dimensions, 5 levels (EQ-5D-5 L) questionnaire (0 to 1) [57]	x		x	
Aerobic capacity*	6-minute walking test [40]	x			
Trunk and lower limb resistance*	Trunk flexor test; Side bridge; Biering-Sörensen test; 60s sit to stand test [41–45]	x			
Trunk and lower limb flexibility*	Sit-and-reach test; Flexion and extension Schober test; Modified Thomas test [46–48]	x			
Motor Control*	Aberrant movement pattern and prone instability test [49, 50]	x			
Health care utilization and LBP Treatments (medical consultations, medication or imaging tests prescribed, referral to other interventions or to other medical specialties or services or sickness certificates) **	Self-reported questionnaire	x	x	x	

*MyBack group only; **Also measured when participants report a LBP recurrence in the screening that occurs every month.

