### Data collection and outcomes

#### #Aim I: effectiveness

Two trained researchers, blind to the patients’ group, will be responsible for the organization and data collection process. Every 30 days after the date of randomization, and over a 1-year period, the participants of both groups will receive a text message (SMS API (twilio.com)) with a yes/no question regarding LBP recurrence (In the last month did you have pain in your back, with an intensity equal or greater than 2, on a scale where “0” means no pain and “10” the worst pain imaginable and lasting at least 24 h?). This question is based on the definition of LBP recurrences: “the return of LBP with a minimum duration of 24 hours, with a pain intensity ≥ 2 on an 11-point numerical scale, preceded by a minimum period of 30 days without pain” [53]. All text messages will be sent and received through a specific SMS platform. In the presence of a LBP recurrence, the researchers will contact the participant by telephone to answer to a brief survey concerning the date of the recurrence and its impact (if the episode was severe enough to limit activity and/ or to cause care seeking), and to fulfil the self-reporting instruments (Table 1).

In the absence of a LBP recurrence, the researchers will contact the participants at three fixed data points: 3, 6 and 12 months after baseline, to fulfil the NPRS, Roland-Morris Disability Questionnaire (RMDQ), Musculoskeletal Health Questionnaire (MSK-HQ) and EuroQol (EQ-5D-3 L) (Table 1). The estimated patient’s burden to answer all the questionnaires is approximately 15 min. In addition, the participants’ medical records will be reviewed every 3 months. Data on any additional medical consultations, medication or imaging tests prescribed, referral to other interventions or to other medical specialities or services or sickness certificates will be recorded on the patient’s CRF.

Participants will remain on the trial unless they choose to withdraw consent, or they fail to answer three consecutive follow-up text messages. To prevent withdrawals and when a participant does not answer to 3 SMS text message or is not available at fixed follow-up time points, a maximum of three additional attempts will be made by telephone call.

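### The recurrence definition and the entry criterion use different pain-free thresholds, and a recurrence in one or two skipped text months is never asked about

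*Protocol article*

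**What the plan says.** **Definition of the event.** The protocol article (Data collection and outcomes, Aim I) defines a recurrence as back pain of at least 2 on the 0-10 scale, lasting at least 24 h and "preceded by a minimum period of 30 days without pain". Table 1 repeats this.

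**Entry criterion.** Under Participants, recovery is "having a pain score of “0” or “1” on a 11-point Numeric Pain Rating Scale (NPRS) for, at least, 30 consecutive days". The article adds that "only participants without pain (or minimal pain – 1/10 NPRS) for at least a month are eligible". The screening text under Recruitment uses the same 0-or-1 rule.

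**Measurement.** Every 30 days for a year a yes/no text asks: "In the last month did you have pain in your back, with an intensity equal or greater than 2", lasting at least 24 h. After a yes, researchers telephone for "a brief survey concerning the date of the recurrence and its impact" and complete the questionnaires.

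**Missed contacts.** Up to three telephone attempts are made "when a participant does not answer to 3 SMS text message or is not available at fixed follow-up time points". Three consecutive unanswered texts end participation. Participants without a recurrence are contacted at 3, 6 and 12 months for pain, disability, musculoskeletal health and quality of life. Medical records are reviewed every 3 months, and missing values are to be multiply imputed (Data handling and analysis plan).

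**Use.** The primary outcome is binary per participant. Days from randomization to first recurrence feed a secondary log-rank comparison.

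**The concern.** Two separate problems bear on who is classified as having a primary event.

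First, the definition and the entry criterion draw the pain-free line in different places. The Participants section itself distinguishes being without pain from minimal pain of 1/10, so it is not safe to assume that the definition's wording silently includes a score of 1. For participants who enter at 1/10, the text and the definition can then give different answers. The data described would not show which participants are affected.

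Second, the outcome covers all 12 months, but a participant who skips one or two texts and then replies is asked only about the latest month. A recurrence confined to the skipped months goes unreported unless it left a trace in the medical record.

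Both problems arise at data collection. An analysis plan written later can choose a rule, but it cannot recover a 30-day history or a month's answer that was never requested. The time-to-first-recurrence analysis inherits both.

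**Working it through.** **1. The plan's own figure.** Inputs from Sample size: 40% versus 20%, alpha 0.05 (two-sided assumed, as sidedness is not stated), power 80%, 1:1 allocation. The pooled two-proportion formula gives

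n = [1.960·√(2·0.30·0.70) + 0.842·√(0.40·0.60 + 0.20·0.80)]² / 0.20² = 81.2, rounded up to 82 per group.

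The plan states 81, at which power is 79.9%. The sample size reproduces; this point is not about a miscalculation.

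**2. Definition against measurement.** Three participants, each with pain of 2 or more for over 24 h in some month and no earlier episode:

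| Preceding 30 days | Eligible history at entry? | Monthly text | Definition, read literally | Definition, if 0-1 counts as pain-free |
|---|---|---|---|---|
| All at 0 | Yes | Case | Case | Case |
| All at 1 | Yes | Case | Not a case | Case |
| Mixed 0 and 1 | Yes | Case | Not a case | Case |

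The readings part only in the second and third rows. To tell those rows from the first, someone must ask whether the preceding 30 days were at 0 or at 1. The text asks about 2 or more; the call, as described, asks about date and impact.

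**3. Coverage of skipped months.** Suppose texts 4 and 5 are unanswered and text 6 is answered.
- Text 6 covers only the month before it.
- The three-text trigger for calls is not reached.
- The 6-month contact collects questionnaires; Table 1 marks recurrences in the monthly column only.
- Record review finds episodes that led to care. The Background puts care-seeking at 40% of people with a recurrence, so most would leave no record.
- Imputation models the missing answer; it does not obtain it.

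**4. Illustration of size.** The documents give no reply rate per text. Assume 5-10% of texts go unanswered, independently of arm and of recurrence, and that no later episode is reported. Then at most 5-10% of first recurrences are lost:
- 5% lost: 0.40 × 0.95 = 38%; 0.20 × 0.95 = 19%.
- 10% lost: 0.40 × 0.90 = 36%; 0.20 × 0.90 = 18%.

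The relative risk is 0.50 in each case. With the planned attrition of 5% + 10%, 93 × 0.85 = 79 per arm are analysed. Power = Φ{[d − 1.960·√(2p̄(1−p̄)/79)] / √[(p₁(1−p₁) + p₂(1−p₂))/79]}, where d = p₁ − p₂ and p̄ is the mean of the two rates:

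| Rates | Calculation | Power |
|---|---|---|
| 40/20% | (0.200 − 0.1429)/0.0712 = 0.80 | 79% |
| 38/19% | (0.190 − 0.1408)/0.0702 = 0.70 | 76% |
| 36/18% | (0.180 − 0.1385)/0.0692 = 0.60 | 73% |

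**The case against.** The strongest reply is that the pieces fit if 0-1 is what the authors mean by pain-free. The outcome is binary, so for each participant it is enough that one episode qualifies. Everyone enters after at least 30 days at 0-1, and the text's cut-off of 2 is the complement of 0-1. Where texts are answered, a run of no replies before the first yes, together with the date taken on the call, documents the preceding interval at the level of 2 or more for 24 h. This stands, and it makes the problem much narrower than a missing criterion. What remains is that the protocol does not say 0-1 is meant, its own gloss separates the two states, and serial no replies cannot distinguish 0 from 1 or exclude spells under 24 h.

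A second reply is that missed months are not ignored: there are calls, fixed contacts, record review and imputation. That is also true, but none of them asks about one or two skipped months.

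A third is that an article condenses the full protocol, so the call script and the handling of a single missed text may be specified elsewhere. That limits how much weight the silence on the call can bear. It does not explain why the printed definition and the printed entry criterion differ, or why the printed question looks back one month only.

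**Conclusion.** The point holds as a mismatch in wording and a gap in coverage for the primary outcome. It should be fixed, but it does not make the endpoint unworkable.

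Stronger conclusions that a reader might infer are not supported:
- **That the primary event count is contradictory.** The outcome is at least one recurrence per participant. If 0-1 is read as pain-free, eligibility, definition and text agree.
- **That a participant at 1/10 can never be a case.** Someone who merely stays at 1/10 answers no to the text. The conflict arises only on a flare to 2 or more, and even on the literal reading it lasts only until 30 days at 0 have passed.
- **That power collapses because participants at 1/10 drop out of the event count.** Removing 20% or 30% of events in both arms would give 66% or 58% power at 79 per arm. But the documents give no share of participants at 1/10, and the calculation applies a criterion that the described text and call do not collect.
- **That about half or more of participants are compromised.** With 5-10% non-response, 46-72% would miss at least one of 12 texts (1 − 0.95¹² and 1 − 0.90¹²). A missed text matters only if the first recurrence falls in that month and no later one is reported.
- **That the loss favours one arm.** Nothing in the documents shows different reply rates.

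The true size is unknown. The illustrated fall in power from 79% to 76-73% rests on assumed non-response of 5-10%, equal loss in both arms, and no recovery through records or later episodes.

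**What to change.** 1. Use one pain-free threshold under Participants, Recruitment, Table 1 and the Aim I outcome definition. NPRS 0-1 matches both the entry criterion and the text's cut-off of 2 or more. Using 0 throughout would also reconcile the wording, but it would change eligibility and the screening text.
2. Add one item to the existing recurrence call confirming the preceding 30 days at that threshold. The screening text already has usable wording.
3. State that the primary event is the first episode meeting that definition, and use the same episode in the time-to-event analysis.
4. Reword the monthly text to ask about pain since the last answered message, giving its date, so that one reply closes any gap.

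The cost is one text template, one call item and a few words of definition. The drawbacks are slightly longer recall after a missed text and, if 0-1 is adopted, a small departure from the wording of the cited definition. The sample size does not need to change.

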The primary outcome of the study will be the risk of LBP recurrence, i.e. the percentage of participants experiencing one or more episodes of LBP recurrence within a 12-month follow-up period. Secondary outcomes include pain intensity, functional disability, musculoskeletal health and HRQoL. Pain intensity will be measured by a NPRS (11-point version). The NPRS has proven to be valid and reliable in patients with LBP [54, 55]. Disability status and HRQoL will be evaluated through the Portuguese versions of the Roland Morris Disability Questionnaire (RMDQ) and the EQ-5D, 5 L. Both self-reported measurement instruments have been cross-culturally validated to Portuguese language and showed good to excellent psychometric properties [56, 57]. The Portuguese version of the Arthritis Research UK Musculoskeletal Health Questionnaire (MSK-HQ) will be used to measured musculoskeletal health and 12 related subdomains (pain severity, physical function, work interference, social interference, sleep, fatigue, emotional health, physical activity, independence, understanding, confidence to self-manage and overall impact). The original and Portuguese version of MSK-HQ showed adequate psychometric properties in people with musculoskeletal pain [58–60].

Costs data will be collected to both groups from medical health records, and they will consist of all back pain-related recourse used within primary health care by each participant. For the MyBack group, the costs related to the MyBack programme (costs per session; costs of training physiotherapists; costs of materials and transport) will also be collected.

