#### #Aim I: effectiveness

To assess the effectiveness of the MyBack programme, a quantitative analysis of primary and secondary outcomes will be made using multivariable regression models. All quantitative analysis will be conducted by a statistician who will be masked to the intervention groups. The analyses will follow the intention-to-treat principle. Between-group differences for the primary outcome (risk of LBP recurrence) will be analysed using relative risk reduction (95%IC and significance level of *p* ≤ 0.05). Secondarily, survival curves for each group will be described and compared (log-rank test) using the days from randomization to the first episode of recurrence. Scores of pain intensity, disability, musculoskeletal health and HRQoL will be assessed for outliers, normality and homogeneity. In the case of parametric distribution, the differences between the two groups over time will be analysed using two-way repeated measures ANOVA. If significant, the Bonferroni post-hoc test will be used. In addition, a subgroup analysis will be performed according to potential differences between the participants who adhered or did not adhere to the experimental intervention.

The cost-effectiveness analysis will be developed from the perspective of the health care provider. All costs will be calculated for each participant and indexed in Euros for the reference year 2023. Quality-adjusted life years (QALYs) will be calculated with the EQ-5D, 5 L. Between-group differences for costs, QALYs and years of life gained will be analysed following the non-parametric bootstrap method. A cost-effectiveness analysis will be conducted using the incremental cost per QALY ratio.

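### The text and Table 1 conflict on whether participants with a recurrence complete the 3-, 6- and 12-month assessments, so secondary outcomes and QALYs may be timed by the primary outcome

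*Protocol article*

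**What the plan says.** The protocol article describes follow-up measurement in two places.

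**Data collection and outcomes, #Aim I: effectiveness.** Every 30 days "the participants of both groups will receive a text message" with one yes/no question about recurrence. Two branches follow. For a positive reply: "In the presence of a LBP recurrence, the researchers will contact the participant by telephone to answer to a brief survey concerning the date" and impact of the episode, and to complete the self-report instruments, for which the text points to Table 1. For the other branch: "In the absence of a LBP recurrence, the researchers will contact the participants at three fixed data points", namely 3, 6 and 12 months, to complete the NPRS, RMDQ, MSK-HQ and EuroQol. No sentence says that a participant with a recurrence is also assessed at the fixed points.

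**Baseline assessment, Table 1.** NPRS, RMDQ, MSK-HQ and EQ-5D are all ticked at 3, 6 and 12 months with no condition. Four rows carry a double asterisk (work situation, pain intensity, functional disability, health care use), explained as "Also measured when participants report a LBP recurrence in the screening that occurs every month". MSK-HQ and EQ-5D do not carry it. Pain and RMDQ are also ticked as monthly.

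The primary outcome is "the percentage of participants experiencing one or more episodes of LBP recurrence within a 12-month follow-up period". The protocol adds: "Secondary outcomes include pain intensity, functional disability, musculoskeletal health and HRQoL". For these scores, if their distribution allows, "the differences between the two groups over time will be analysed using two-way repeated measures ANOVA", under intention to treat. QALYs are to come from the EQ-5D.

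**The concern.** Recurrence occurs after randomisation, and the programme is meant to prevent it. If it decides who is assessed at a fixed time, or when, the two arms are no longer compared like with like. A comparison at 12 months among recurrence-free participants leaves out those in whom a preventive benefit on disability or quality of life would mostly appear. Filling the gap with scores from the recurrence call mixes event-timed with scheduled values, in different proportions by arm.

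Repeated-measures ANOVA needs common times. QALYs need EQ-5D scores at known times for everyone randomised. The cost per QALY would inherit any error.

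An analysis plan cannot repair this afterwards, because it cannot recover scores that were not collected. The multiple imputation foreseen under Data handling and analysis plan would have little to work from: if MSK-HQ and EQ-5D stop at a recurrence, no observed post-recurrence values inform the imputed ones.

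**Working it through.** **1. The two sources side by side**

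| Item | Data-collection text | Table 1 |
|---|---|---|
| 3, 6, 12 months | in the absence of a recurrence | everyone, no condition |
| Instruments at a recurrence | self-report instruments, by reference to Table 1 | marked rows only; not MSK-HQ or EQ-5D |
| Monthly contact for all | one yes/no text message | also NPRS and RMDQ |

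Taking the condition from the text and the markings from the table, a participant with a recurrence has no clearly scheduled MSK-HQ or EQ-5D after baseline.

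**2. Inputs.** The Sample size section gives 40% recurrence in usual care, 20% with MyBack, alpha 0.05, power 80% and 81 per group. With two-sided alpha (assumed) and pooled variance:

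n = [1.960 × √(2 × 0.30 × 0.70) + 0.842 × √(0.24 + 0.16)]² / 0.20² = 81.2

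This reproduces the stated 81 (82 if rounded up; power at 81 is 79.9%). The figure is not in dispute and only supplies the risks used below.

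**3. Coverage of the fixed assessments, worst-case reading (no recurrence so far), before dropout.** Share assessed = 1 − cumulative recurrence.

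- 12 months, usual care: 1 − 0.40 = 60%, or 81 × 0.60 = 48.6 participants.
- 12 months, MyBack: 1 − 0.20 = 80%, or 81 × 0.80 = 64.8.
- Together: 113.4 of 162, or 70%.
- With a constant hazard (assumption), 0.60^(t/12) and 0.80^(t/12) give 88% and 95% at 3 months, and 77% and 89% at 6 months.
- The Background gives 1-year recurrence of 33% to 70%. With a relative risk of 0.5 throughout (assumption), the 12-month shares run from 67% and 84% to 30% and 65%.

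**4. Coverage on the milder reading (no recurrence at that month's screening).** With the same constant hazard, the chance of a first recurrence in a given month is 1 − 0.60^(1/12) = 4% in usual care and 1 − 0.80^(1/12) = 2% with MyBack. Only about these shares of those still recurrence-free would be diverted at any one fixed visit. Repeat episodes would add some.

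**5. Size of the possible bias.** Let D be the mean gap at 12 months between participants who have and have not had a recurrence, equal in both arms, with no other treatment effect (assumptions).

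- All randomised: difference between arms = (0.40 − 0.20) × D = 0.20 × D.
- Recurrence-free only: difference = 0.
- RMDQ, D of 2, 4 and 6 points: 0.4, 0.8 and 1.2 points lost.
- EQ-5D, D of 0.05, 0.10 and 0.20: 0.01, 0.02 and 0.04 lost.

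If scores from the recurrence call are put in place of the fixed-time scores and their gap is a larger D*, the difference becomes 0.20 × D*. The benefit is then overstated by 0.20 × (D* − D). The direction of the error therefore depends on how the gap is handled.

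**The case against.** The strongest reply is that everyone was probably meant to be assessed.

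- Table 1 sets no condition, and its footnote presents the recurrence measurements as additional.
- A recurrence does not end participation. The text plans reminder calls for anyone unavailable at the fixed time points, without mentioning recurrence.
- The analysis is by intention to treat.
- Apart from the recurrence row itself, the rows ticked monthly are exactly the double-asterisk rows, so those ticks may be shorthand for the recurrence trigger.

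All of this stands. It limits the point to a conflict between text and table. It does not remove the conflict, because the sentence that tells assessors what to do carries the condition.

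Four stronger readings are tempting, and the documents do not support them:

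- A reader might infer that the fixed assessments are made exclusively in recurrence-free participants. The text does not say so, and Table 1 points the other way.
- A reader might infer that participants with a recurrence have no follow-up MSK-HQ or EQ-5D. The recurrence call refers to the self-report instruments of Table 1 without restriction, which can include both.
- A reader might treat the scores from the call as taken at the height of the episode. The message asks about the past month, so the call may come weeks after onset, possibly after recovery.
- A reader might take the 60% and 80% as the expected coverage. They hold only if absence means no recurrence so far.

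The gap D may also be small at a fixed visit: the Background states that 90% of patients recover within 6 weeks, so many early recurrences would have resolved by 12 months. That is why a range is shown.

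**Conclusion.** The conflict is real and should be fixed for the secondary and economic outcomes. The documents do not settle whether participants with a recurrence complete the fixed assessments, nor which instruments they complete at the recurrence call. If the text is followed literally, measurement depends on the primary outcome.

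The size depends on the reading. At worst, 12-month coverage is about 60% against 80%, with a loss of 0.20 × D: 0.4 to 1.2 RMDQ points for assumed gaps of 2 to 6. On the month-by-month reading, about 4% and 2% of those still recurrence-free are diverted at a visit, and the effect is much smaller. The values of D, its equality across arms and the constant hazard are assumptions, not figures from the protocol.

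The primary outcome, its relative-risk analysis, the time-to-recurrence comparison and the sample size are unaffected.

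**What to change.** 1. In the data-collection text, state that all randomised participants complete the NPRS, RMDQ, MSK-HQ and EQ-5D at 3, 6 and 12 months, whether or not they have had a recurrence.
2. State that scores from recurrence-triggered calls are additional data and do not replace the fixed-time scores in the group comparisons or the QALYs.
3. Align Table 1 with the text: the monthly ticks for NPRS and RMDQ, and the double-asterisk marks, should show exactly which instruments are taken at a recurrence.

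The cost is a wording change and some extra calls. With equal arms, (40% + 20%) / 2 = 30% of participants are expected to have a recurrence, or 0.30 × 186 ≈ 56. At most three extra contacts each, at the protocol's own estimate of about 15 minutes, come to 56 × 45 minutes = 42 hours over the whole trial, by staff already making such calls.

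### The protocol names EQ-5D-3L for the 3, 6 and 12 month contacts but EQ-5D-5L in Table 1, the outcome definition and the QALY calculation

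*Protocol article*

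**What the plan says.** The EQ-5D version is named in four places in the protocol article.

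- **Data collection and outcomes, Aim I** (contacts at 3, 6 and 12 months, for participants without a recurrence): "Musculoskeletal Health Questionnaire (MSK-HQ) and EuroQol (EQ-5D-3 L"). This is the three-level version, and the sentence points to Table 1.
- **Baseline assessment, Table 1**: "EuroQol, 5 dimensions, 5 levels (EQ-5D-5 L) questionnaire (0 to 1) [57"]. This is the five-level version, in a single row marked for baseline and for 3, 6 and 12 months.
- **Data collection and outcomes, Aim I** (secondary outcomes): disability and quality of life are measured with the "Portuguese versions of the Roland Morris Disability Questionnaire (RMDQ) and the EQ-5D, 5 L".
- **Data handling and analysis plan, Aim I**: "Quality-adjusted life years (QALYs) will be calculated with the EQ-5D, 5 L".

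Two further statements bear on the point. When a recurrence is reported, participants are telephoned about the episode "and to fulfil the self-reporting instruments (Table 1"). The only EQ-5D in that table is the five-level one, but its row lacks the double asterisk that marks measures repeated at a recurrence. For the economic comparison, the analysis plan says: "Between-group differences for costs, QALYs and years of life gained will be analysed following the non-parametric bootstrap method". It does not say whether that comparison is adjusted for baseline utility.

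**The concern.** The odd mention sits in the sentence that tells data collectors which form to use at follow-up, so a slip there can reach the data. The two versions have different response levels and need different value sets. Three-level answers would need a three-level value set or a mapping onto the five-level scale, and either is a different calculation from the one stated. A form used in error cannot be replaced once the visit has passed.

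Two outputs are exposed: health-related quality of life, a named secondary outcome to be compared over time, and the incremental cost per QALY, the stated cost-effectiveness measure.

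The condition attached to the three-level sentence adds a further risk. It applies to participants without a recurrence, while those with one are sent to the Table 1 instruments. Read literally, the version could follow recurrence status, which is the primary outcome and is expected to differ between arms.

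**Working it through.** **Plan's own figures.** The article gives no figure for the QALY analysis. The recurrence proportions used below come from the Sample size section: 40% under usual care and a relative risk of 0.50, hence 20% under MyBack. With two-sided alpha 0.05 and 80% power, the pooled-variance formula gives 82 per group against the stated 81 (power at 81 is 79.9%). Also, 81 × 1.15 = 93.15, the stated 93. These inputs are coherent.

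**Weights.** With utility measured at 0, 3, 6 and 12 months and QALYs taken as the trapezoidal area (an assumption; the article does not name the rule), the weights in years are:

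- 0 months: 0.25/2 = 0.125
- 3 months: (0.25 + 0.25)/2 = 0.25
- 6 months: (0.25 + 0.50)/2 = 0.375
- 12 months: 0.50/2 = 0.25

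The follow-up weights sum to 0.875.

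**Version shift.** The documents give no 3L/5L difference. I assume a constant shift d of 0.02 to 0.08 in utility.

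*Case A: five-level at baseline, three-level for everyone at follow-up.*
- Each arm's mean QALY moves by 0.875 × d = 0.0175 to 0.07.
- The between-group difference moves by 0.875 × d − 0.875 × d = 0.
- Mean change from baseline in utility moves by d in each arm, so the time effect in the planned repeated-measures ANOVA would be confounded with the instrument.

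*Case B: three-level without a recurrence, five-level with one.*
- Proportion on the three-level form: 80% under MyBack and 60% under usual care, a difference of 0.20.
- If this applied at all three follow-ups, the QALY difference would move by 0.20 × 0.875 × d = 0.0035 to 0.014. This is an upper limit, because it treats every participant with a recurrence as on the five-level form from 3 months.
- If it applied only at 12 months: 0.20 × 0.25 × d = 0.001 to 0.004.
- The direction depends on which version scores higher, which the documents do not say.

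**Scale and precision.** Assume a utility SD of 0.10 to 0.20, a correlation of 0.5 between any two time points, and 93 per arm.

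- SE of the baseline difference: SD × √(2/93) = 0.0147 to 0.0293.
- Variance of an individual QALY in units of SD²: 0.5 × (0.125² + 0.25² + 0.375² + 0.25²) + 0.5 × 1² = 0.641. Its square root is 0.800.
- SE of the unadjusted QALY difference: 0.800 × (0.0147 to 0.0293) = 0.012 to 0.023.
- Covariance of QALY with baseline in the same units: 0.125 + 0.5 × 0.875 = 0.5625. Residual variance after adjustment: 0.641 − 0.5625² = 0.324, square root 0.569.
- SE of the adjusted QALY difference: 0.569 × (0.0147 to 0.0293) = 0.008 to 0.017.

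The largest Case B shift is thus of the same order as the standard error of the comparison. Baseline adjustment would cut that standard error by about 29% (1 − 0.569/0.800).

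**The case against.** The strongest reply is that this is a typing slip. The five-level version is named three times and the three-level once, and the three-level sentence defers to a table that says five-level at those very visits. That stands: the article conflicts over the follow-up version, and it does not plan a change of instrument. A reader might infer a designed split, with five-level at baseline and three-level afterwards. Table 1 rules that out.

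A reader might also infer that the version problem by itself creates a spurious QALY difference or decides its sign. Case A shows that a constant shift common to both randomised arms cancels. Distortion needs version use that differs by arm, for example through recurrence status, or a shift that varies with health state. The article states no expected QALY gain, so an effect on the sign cannot be shown. Case B is also only one reading, since Table 1 marks the fixed visits without any recurrence condition.

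Finally, a reader might take the bootstrap sentence to mean that QALYs will be compared without baseline adjustment. The article neither states nor excludes this. Bootstrapping is compatible with a regression-adjusted estimate, and the covariates may be set in a fuller plan that is not shown. Chance imbalance under randomisation is sampling variation, already reflected in the bootstrap uncertainty. That is not a finding.

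What survives is the contradiction itself. It is in current text, it concerns which form is handed out, and a fuller analysis plan would not remove it.

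**Conclusion.** The point holds as an inconsistency to be reconciled. Following the data-collection sentence would prevent QALYs from being scored on the five-level version as planned, and would confound change from baseline in quality of life with the instrument.

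The effect on the between-group QALY difference is nil for a constant shift common to both arms. It is at most 0.0035 to 0.014 if the version tracks recurrence status at the planned 40% against 20%. That range rests on an assumed version shift of 0.02 to 0.08, trapezoidal QALYs, and recurrence-dependent use at all three follow-ups. None of these is given in the documents.

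The primary outcome is unaffected. The matter should still be settled, because it governs a secondary outcome and the cost-per-QALY result and is cheap to correct.

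**What to change.** 1. In Data collection and outcomes (Aim I), change the three-level mention to EQ-5D-5L, in line with Table 1, the outcome definition and the QALY calculation.
2. Confirm which forms are in use. If any three-level forms have been completed, record for whom and when, so that their scoring can be decided before the arms are compared.
3. State that one version and one value set apply at baseline, 3, 6 and 12 months, regardless of recurrence. Clarify whether the EQ-5D is also completed at a recurrence, since the text and the Table 1 marks do not settle it.
4. Optional, for precision only: estimate incremental QALYs by regression on arm, baseline EQ-5D utility and health unit, resampling participants within arm and bootstrapping jointly with costs.

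The cost is a one-word correction, a check of the forms, a clarifying sentence, and, if item 4 is taken up, covariates that are already collected.
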